**Figure 1 fig1:**
[figure not shown]
CONSORT flow diagram showing participant progression through screening, allocation, follow-up, and analysis Adapted from CONSORT, 2010 (18, 39). License: Open Access/Public Domain. Source: consort-statement.org.

**Figure 2 fig2:**
[figure not shown]
Randomization and allocation workflow diagram. Operational workflow for participant randomization and allocation using stratified block randomization. Original diagram created by [name].

### Intervention Arms

2.10

Participants will be randomly allocated to one of three intervention arms of increasing intervention intensity.

*Arm 1 (active control)*: participants will receive routine HIV promotion messages broadcast through the partner FM radio station.

*Arm 2 (standard digital messaging)*: participants will receive the FM radio intervention together with standardized HIV related WhatsApp messages delivered through closed WhatsApp study group.

*Arm 3 (peer influencer intervention)*: participants will receive the FM radio intervention, standardized WhatsApp messaging, and additional engagement from trained online peer influencers who will facilitate discussions, share structured HIV testing messages, provide behavioral prompts and reminders, answer general questions, and encourage HIV testing at the partner HIV Testing Services (HTS) facility.

Interventions will be delivered over a 12-week period.

### Online peer influencer intervention

2.11

A total of 15 online peer influencers (five per age stratum) will be identified using social network analysis (SNA) methods. This approach enables objective selection of individuals with high influence within digital networks, improving intervention reach and effectiveness compared to convenience-based peer educator models (25).

Peer influencers will complete standardized virtual training covering HIV communication, ethical conduct, participant engagement, confidentiality, and referral procedures. Throughout the intervention they will receive ongoing supervision, weekly monitoring, and fidelity assessments.

Peer influencers will facilitate WhatsApp discussions, encourage HIV testing, distribute referral information, and support participant engagement. They will not participate in recruitment, randomization, outcome assessment, or data analysis (44).

### Contamination prevention

2.12

To minimize contamination, each study arm will operate within separate closed WhatsApp groups. Participants will have no interaction across study arms, and peer influencers will communicate only with participants assigned to their respective intervention group.

Potential contamination will be assessed during process evaluation (26).

### Masking

2.13

Because of the behavioral nature of the intervention, participants and peer influencers cannot be blinded.

Outcome verification will be conducted independently wherever feasible, while data analysts will analyze masked treatment codes until completion of the primary analyses.

This partial masking approach is consistent with best practices for non pharmacologic trials and is intended to reduce ascertainment and analytical bias (27) (see Figure 3).

**Figure 3 fig3:**
[figure not shown]
SPIRIT schedule of enrollment, allocation, interventions and assessments. Adapted Chan et al., SPIRIT 2013 Statement (19). License: Open Access/Creative Commons CC BY-NC-ND. Source: spirit-statement.org.

### Compensation

2.14

Peer influencers will receive reimbursement for reasonable internet data and communication costs incurred during the study. No payment will be provided for participation time, and compensation will not constitute an inducement to participate. This compensation is intended to support participation without constituting undue inducement, in line with ethical research guidelines (28).

### Outcome measures

2.15

#### Primary outcome

2.15.1

The primary outcome is HIV testing uptake, defined as completion of at least one HIV test during the 12 week follow up period after randomization, irrespective of HIV test result.

#### Secondary outcomes

2.15.2

Secondary outcomes include:

Time to first HIV testRepeated HIV testing uptake over timeDifferences between age strataParticipant engagementIntervention acceptabilityLinkage to HIV careCost effectiveness

Qualitative outcomes will be explored through focus group discussions and key informant interviews analyzed using thematic analysis.

### Outcome verification

2.16

PEach participant will receive a Unique Referral Identification Code (URIC) for enrolment. The URIC is a unique study generated identifier that anonymously links participant self reports with partner health facility records without recording personal identifiers in the research database.

Participants will present their URIC whenever attending the partner HTS facility for HIV testing. Facility staff will record the URIC together with confirmation that HIV testing was completed.

HIV testing uptake will be verified using three complementary data sources:

Participant self report;Anonymized partner facility HIV testing records; andURIC redemption.

A participant will be classified as having completed HIV testing only after facility verification confirms test completion. This hybrid verification model minimizes outcome misclassification, reduces recall bias, strengthens internal validity, and preserves participant confidentiality (29). This approach improves validity by reducing reliance on self report alone and is consistent with best practices in behavioral intervention trials (29).

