**Methods:**

A three-arm, age-stratified randomized controlled trial (1:1:1 allocation) will recruit young adult men aged 18–32 years online in Nairobi. Participants will receive either (i) FM radio HIV messaging, (ii) FM radio plus standard WhatsApp HIV messaging, or (iii) FM radio plus WhatsApp messaging with an online peer influencer intervention. Participants will be followed for 12 weeks. The primary outcome is verified HIV testing uptake, defined as completion of at least one HIV test during follow up and confirmed through participant self report, de-identified facility records, and a Unique Referral Identification Code (URIC). Primary analyses will use generalized linear mixed models under an intention-to-treat framework, with prespecified secondary analyses.

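### The primary outcome has four case definitions that do not match, and a partner-facility test counts only if the referral code is recorded, so capture could differ by arm

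*Protocol article*

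**What the plan says.** All references are to the protocol article. Four places say what makes a man a tester:

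- Abstract, Methods: the outcome is verified testing, "confirmed through participant self report, de-identified facility records, and a Unique Referral Identification Code (URIC").
- 2.15.1 Primary outcome: "completion of at least one HIV test during the 12 week follow up period after randomization, irrespective of HIV test result". No place of testing and no verification is required.
- 2.16 Outcome verification: "HIV testing uptake will be verified using three complementary data sources", namely self-report, anonymized partner-facility records and URIC redemption. The deciding sentence follows: "A participant will be classified as having completed HIV testing only after facility verification confirms test completion".
- 2.17.1 Survey instrument: the primary outcome is measured by electronic questionnaire at each follow-up, with a yes/no item on testing in the past 4 weeks.

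On linkage, 2.16 says the URIC "anonymously links participant self reports with partner health facility records without recording personal identifiers in the research database". It expects that "Participants will present their URIC whenever attending the partner HTS facility for HIV testing", and that "Facility staff will record the URIC together with confirmation that HIV testing was completed". Section 2.18 repeats that facility data are linked by the URIC.

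On the arms, 2.10 gives Arm 1 radio messages only and places the influencers in Arm 3, where they encourage testing at the partner facility. Section 2.11 adds: "Peer influencers will facilitate WhatsApp discussions, encourage HIV testing, distribute referral information, and support participant engagement". The Discussion lists as a limitation that tests done outside participating facilities may be missed.

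**The concern.** The primary endpoint should classify every man the same way whichever section is read. Here the same man can be tested, untested or missing.

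The description of three complementary sources also suggests more cross-checking than the design provides. An anonymized facility record cannot be tied to a participant without the code, so the record and the redemption succeed or fail together. A real test at the partner facility is lost if the code is not presented or not written down. The Discussion does not acknowledge this loss, because its limitation concerns tests done elsewhere.

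If that loss were equal across arms, it would only dilute the effect. If Arm 3 is better reminded of the code and of the facility, recorded uptake can differ with identical testing. The same holds for survey response, should self-report be required. A larger sample would not remove such a bias.

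**Working it through.** **1. The four definitions, applied to three men who all tested within 12 weeks.** The Abstract is read literally here.

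| Man | Abstract | 2.15.1 | 2.16 | 2.17.1 |
|---|---|---|---|---|
| Tested at partner facility, code recorded, no survey returned | not confirmed | tested | tested, if facility verification suffices | missing |
| Tested at partner facility, code not recorded, survey says yes | not confirmed | tested | untested (record cannot be linked) | tested |
| Tested elsewhere, survey says yes | not confirmed | tested | untested | tested |

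No row agrees across all four columns. The second row is the loss at issue here. The third is the one the Discussion acknowledges.

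**2. The plan's own sample size.** 1.96² × 0.25 / 0.05² = 384.16, and 384 / 0.82 = 468.3, so 468 (156 per arm) reproduces. The two-proportion formula in 2.8 at 20% v 40% gives (1.96 + 0.84)² × (0.16 + 0.24) / 0.20² = 78.4, or 79 per arm. Power at 156 per arm is about 97%. The sample size is therefore not in question.

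**3. Unequal capture with no true difference.** Inputs: 156 per arm and two-sided 0.05 (2.8); true uptake 20%, the control assumption in 2.8, and 30% as an alternative; capture rates assumed, since the article gives none. Observed uptake = true uptake × capture, with no false positives. The rejection rate is that of a pooled two-proportion z-test, a simplification of the planned mixed model:

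P(reject) = 1 − Φ[(1.96·se₀ − d)/se₁] + Φ[(−1.96·se₀ − d)/se₁]

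Here d is the observed gap, se₀ the pooled standard error and se₁ the unpooled one.

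Worked case, 20% true uptake and capture 70% v 90%: observed 0.14 v 0.18, d = 0.04. se₀ = √(2 × 0.16 × 0.84 / 156) = 0.0415. se₁ = √((0.1204 + 0.1476)/156) = 0.0414. The upper tail is 0.159 and the lower 0.002, together 16.1%.

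| True uptake, both arms | Assumed capture | Observed | False gap | Rejection rate |
|---|---|---|---|---|
| 20% | 80% v 90% | 16% v 18% | 2 points | 7.6% |
| 20% | 70% v 90% | 14% v 18% | 4 points | 16.1% |
| 30% | 80% v 90% | 24% v 27% | 3 points | 9.3% |
| 30% | 70% v 90% | 21% v 27% | 6 points | 23.6% |

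With equal capture the rate is 5%.

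**4. Equal capture with a true 20% v 40%.** At 80% capture the observed rates are 16% v 32% and power is 91.5%. At 60% they are 12% v 24% and power is 79.1%. Power stays at or above the planned 80% unless about 40% of testers are lost.

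**The case against.** The strongest reply is that 2.16 already holds a usable rule. Facility verification decides, staff record the code with the confirmation, and self-report is not named as a condition. On that view the Abstract merely condenses a list of sources, and 2.15.1 defines the event while the next section defines its verification. Handling of a forgotten code may sit in the Data Management Plan or the SAP, neither of which is shown.

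Much of this stands. A reader might infer that the three sources cannot be combined into any workable rule; 2.16 shows that they can. A reader might also infer that the Abstract strictly demands all three sources; its wording allows that but does not compel it. What the reply does not resolve is 2.17.1, which says the primary outcome is measured by questionnaire. That conflicts with 2.16 inside the article itself, and no document held elsewhere removes it.

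Three further inferences go beyond the text:

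- That no identifiers are kept. Section 2.18 says they are stored separately from research data. What holds is only that the URIC is the sole link described.
- That the code is issued once and never repeated. Section 2.16 says each man receives one for enrolment and is silent on reminders.
- That Arm 3 will be better retained, or that its influencers resend codes. Section 2.11 speaks of referral information without naming the URIC, and the retention reminders in 2.17.5 are not limited to one arm.

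**Conclusion.** The point holds as an inconsistency in the case definition, combined with an unacknowledged route to misclassification. The Abstract, 2.15.1, 2.16 and 2.17.1 do not agree. With the URIC as the only described link, a partner-facility tester whose code is not recorded counts as untested.

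Differential capture in favour of Arm 3 is a plausible risk, not a demonstrated bias. It rests on influencers being present in Arm 3 alone and on their directing men to the partner facility. Its size depends wholly on assumed capture rates: at 70% v 90%, false rejection is about 16% at 20% true uptake and about 24% at 30%; at 80% v 90%, about 8% and 9%. Equal loss costs little power unless it is heavy. The change is worth making before outcomes are classified.

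**What to change.** State one rule in the Abstract, 2.15.1, 2.16 and 2.17.1: a man is tested if a partner-facility record bears his URIC and is dated within 12 weeks of randomization. Self-report is not required and serves only as a secondary or sensitivity outcome. Section 2.17.1 should then no longer say that the questionnaire measures the primary outcome.

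Resend the URIC one-to-one to every participant in all arms on the same dates, for example with each survey link.

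Report by arm the number of self-reported partner-facility tests with no URIC redemption, and run a sensitivity analysis that counts them as tested. The item printed in 2.17.1 does not ask where the test was done, so a place-of-test item is needed if the full questionnaire lacks one.

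The cost is wording in four places, an automated message, possibly one survey item and one extra analysis. There are three drawbacks. The resend is a mild extra prompt to test, though equal in all arms. The sensitivity analysis depends on survey response and so cannot replace the primary rule. The rule also makes explicit that the outcome is testing at the partner facility; tests done elsewhere remain uncounted, as the Discussion already concedes.

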#### Hybrid online-to-facility model

2.4.4

The study employs a hybrid online-to-facility intervention model in which HIV testing demand is generated on WhatsApp, while HIV testing, verification, and linkage to care occur through the participating partner HTS facility (1, 21). This model seeks to address the persistent gap in linkage to care by encouraging participants to access confirmatory HIV testing and HIV care through the partner HTS facility (2, 7). Participants assigned to the intervention arm will be encouraged by trained online peer influencers to attend the partner HTS facility for HIV testing and linkage to care where appropriate.

The hybrid model combines:

*Digital delivery:* Recruitment, screening, informed consent, enrolment, randomization, intervention delivery, follow up, and participant engagement via WhatsApp*Facility based services:* HIV testing, confirmatory testing where required, referral code redemption, outcome verification, and linkage to care

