#### Survey instrument

2.17.1

The primary outcome will be measured using standardized electronic questionnaires administered at each follow up assessment.

Participants will be asked:

*“At any time during the past 4 weeks, have you had an HIV test?”*

Responses will be recorded as Yes or No.

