## Discussion

3

This protocol describes a three-arm, age-stratified randomized controlled trial evaluating whether adding an online peer influencer led WhatsApp intervention to standard FM radio and WhatsApp HIV messaging increases HIV testing uptake among young adult men in Nairobi, Kenya. The study combines digital demand generation with facility based HIV testing verification using a Unique Referral Identification Code (URIC), providing an objective approach to outcome measurement while preserving participant confidentiality.

The trial addresses an important evidence gap by evaluating the additional value of online peer influencer engagement beyond existing HIV communication strategies (46). Methodological strengths include randomized allocation, age stratification, repeated outcome assessments, intention-to-treat analysis, objective verification of HIV testing uptake, and implementation in a real world urban setting (50).

Several limitations should be acknowledged. Blinding of participants and peer influencers is not feasible because of the behavioral nature of the intervention and may introduce performance bias (27). In addition, recruitment through online platforms may limit participation among individuals with limited internet access, potentially affecting generalizability (54). Although facility based verification strengthens outcome validity, HIV tests completed outside participating facilities may not be captured despite participant self report (18, 59).

If effective, this intervention could provide a scalable, low cost digital strategy for increasing HIV testing uptake among young men and inform national HIV prevention programmes in Kenya and other comparable settings (2, 7, 24, 47).

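### Tests count only if verified at the partner facility, and active encouragement to test there is described only for Arm 3, so a shift in test site could pass for increased uptake

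*Protocol article*

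**What the plan says.** **What is defined.** Primary outcome (2.15.1) asks for "completion of at least one HIV test during the 12 week follow up period after randomization, irrespective of HIV test result", with no restriction on where the test is done. The abstract calls the same outcome verified uptake, confirmed by self-report, facility records and the URIC.

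**What is counted.** Outcome verification (2.16) lists three sources: self-report, "Anonymized partner facility HIV testing records", and URIC redemption. It then sets the deciding rule: "A participant will be classified as having completed HIV testing only after facility verification confirms test completion". Redemption is tied to one kind of place: "Participants will present their URIC whenever attending the partner HTS facility for HIV testing". Survey instrument (2.17.1) puts it differently: "The primary outcome will be measured using standardized electronic questionnaires administered at each follow up assessment".

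**Where verification happens.** Partner facility (2.4.3) describes one Level 2 facility in Kibra and calls it the primary verification site. Section 2.4.4 also uses the singular. Data management (2.18) and the Discussion use plurals, but no second site is named. The target population (2.5.1) is the whole of Nairobi County, and 2.4.1 says that the county has many accredited testing sites.

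**Who is directed there.** Section 2.4.4 states: "Participants assigned to the intervention arm will be encouraged by trained online peer influencers to attend the partner HTS facility". In Intervention Arms (2.10), the task to "encourage HIV testing at the partner HIV Testing Services (HTS) facility" appears under Arm 3 only. The descriptions of Arms 1 and 2 do not mention the facility. Every participant receives a URIC.

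**What is conceded.** The Discussion grants that "HIV tests completed outside participating facilities may not be captured despite participant self report". It does not say that this loss can differ by arm, and 2.16 presents the method as one that keeps misclassification to a minimum.

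**The concern.** The counting rule is the same in every arm, but its sensitivity need not be. A man who tests at another Nairobi site, or tests himself at home, scores as untested under 2.16. If Arm 3's influencers succeed in moving men to the one place where a test can be verified, a larger share of Arm 3's tests will count, even if no more men test.

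The trial would then report relocated testing as increased testing. The error favours the experimental arm on the primary outcome. It affects Arm 3 v Arm 1 and also Arm 3 v Arm 2, which is the contrast in the stated objective. The Discussion treats missed outside tests as a general limitation. A loss that is equal across arms mainly costs power, whereas a loss that differs by arm can create an effect.

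**Working it through.** **Inputs from the protocol (2.8):** two-sided alpha 0.05, 80% power, 20% uptake in the control arm, 40% in the intervention arms, 468 men in total, 156 per arm.

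**Inputs that are assumed:** true any-site uptake, and the share of tests done at the partner facility in each arm. The protocol gives neither share, so a range is shown.

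**1. The plan's own figures.**
- Cochran's formula: 1.96² × 0.25 / 0.05² = 384.2, taken as 384. Then 384 / 0.82 = 468.3, taken as 468, which is 156 per arm.
- Two-proportion formula: (1.96 + 0.84)² × (0.20 × 0.80 + 0.40 × 0.60) / 0.20² = 7.84 × 0.40 / 0.04 = 78.4, so 79 per arm.
- At 156 per arm, power for 20% v 40% is about 97% (97.4% with pooled variance).

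These figures reproduce, so the point does not rest on a sample-size error.

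**2. Unequal capture with no true effect.** Verified uptake = true uptake × share of tests at the partner facility. Take 30% true uptake in both arms and n = 156 per arm. For the unpooled two-proportion z-test,

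SE = √{[p₁(1 − p₁) + p₂(1 − p₂)] / 156}, z = |p₂ − p₁| / SE, P(significant) = Φ(z − 1.96) + Φ(−z − 1.96).

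| Capture, comparator v Arm 3 | Verified uptake | SE | z | P(significant) |
|---|---|---|---|---|
| 50% v 50% | 15% v 15% | 0.0404 | 0 | 5% |
| 50% v 60% | 15% v 18% | 0.0420 | 0.71 | 11% |
| 50% v 70% | 15% v 21% | 0.0434 | 1.38 | 28% |
| 40% v 60% | 12% v 18% | 0.0403 | 1.49 | 32% |
| 30% v 80% | 9% v 24% | 0.0412 | 3.64 | 95% |

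Exact binomial calculations with the pooled test and other assumed values show the same pattern:
- True uptake 20%, capture 80% v 90%: 7.4%.
- True uptake 40%, capture 70% v 90%: 33%.
- True uptake 40%, capture 50% v 100%: the verified rates are exactly the planned 20% v 40%, and the test is significant 97.5% of the time. In that extreme case a change of site alone reproduces the whole planned effect.

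**3. Equal capture with the planned effect (conditional).** If 20% and 40% are any-site rates and half of all tests are captured in every arm, verified uptake is 10% v 20%.
- n = 156: SE = √[(0.09 + 0.16) / 156] = 0.0400, z = 2.50, power about 70%.
- n = 128 (384 / 3, the number before the attrition allowance): SE = 0.0442, z = 2.26, power about 62%.

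If 20% and 40% are already verified rates, power stays at about 97% and this step does not apply. Section 2.8 does not say which is meant.

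**The case against.** **All arms are linked to the facility.** Every participant holds a URIC, and 2.4.4 also says, without naming an arm, that the model encourages participants to use the partner facility for confirmatory testing and care. The content of the Arm 1 broadcasts and Arm 2 messages is not reproduced in the article. This stands in part. A reader might infer that Arms 1 and 2 get no route to the facility, and the document does not support that. It does describe active encouragement from influencers for Arm 3 alone, and holding a code is not the same as being urged to use it over 12 weeks.

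**There may be more than one verifying site.** The plurals in 2.18 and the Discussion, and the word primary in 2.4.3, allow this. No other site is described, so the passages need reconciling, and a single site should not be taken as settled.

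**The endpoint is verified uptake by design.** The abstract says so and agrees with 2.16. The Introduction and 2.4.4 give poor linkage after self-testing as a reason for the online-to-facility model, so leaving out home tests may be deliberate. On that reading part of the fault is labelling. The objective and Discussion nevertheless speak of HIV testing uptake, not of testing at one clinic.

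**The site shares are invented.** They are assumptions, and small gaps do little: 50% v 60% takes the false-positive rate only to about 11%. The calculation also uses a two-proportion test and not the planned mixed model. This limits what can be said about size, but not about direction.

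**Self-reports and sensitivity analyses are already planned.** The survey item in 2.17.1 does not ask where the test was done, so as quoted it cannot separate more testing from relocated testing. The trial is also unblinded, and self-report may itself be inflated in Arm 3, so it cannot settle the matter alone.

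**Conclusion.** The concern holds as a risk of differential ascertainment in favour of Arm 3. Its direction follows from 2.4.4, 2.10 and 2.16 taken together, provided that encouragement to use the facility works to some degree. Its size cannot be known from the document. Under the assumed 30% true uptake and 156 per arm, the false-positive rate runs from about 11% for a 10-point capture gap, through 28% to 32% for a 20-point gap, to 95% for a 50-point gap.

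Two stronger readings are tempting and are not supported. The document does not show that a positive result would be spurious, because the gap may be small. Nor does it show that the trial is underpowered: the fall to about 70% or 62% needs the planned rates to be any-site rates and half of all tests to be missed.

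As written, a positive primary result could not tell more testing from testing moved to the partner site. This should be corrected before enrolment, because test-site data not collected during follow-up would be hard to recover.

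**What to change.** 1. At randomisation, send every arm the same URIC text, naming the partner facility and explaining how to redeem the code.
2. Add the site and date of each reported test to every follow-up survey.
3. Prespecify, as a required companion to the primary analysis, any HIV test at any site by week 12 (verified or self-reported). Report the partner-site share of reported tests by arm.
4. Describe the primary result as facility-verified testing at the partner site. Extend it to overall testing uptake only with the companion result shown beside it, and note that self-report is unblinded and may be inflated in Arm 3.
5. Align the abstract, 2.15.1, 2.16 and 2.17.1 to one outcome definition, and reconcile 2.4.3, 2.4.4, 2.18 and the Discussion on the number of verifying facilities. State in 2.8 whether 20% and 40% are verified or any-site rates.

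The cost is one standard message, one or two survey items, one further analysis and some editing. The drawbacks are that the companion analysis includes unverified self-report, and that naming the facility to all arms may slightly raise uptake in the control arm.
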